## Discussion

There are a number of factors that support the feasibility of this proposed trial. First, the Investigators have successfully undertaken a number of previous studies of therapeutic interventions in critically ill patients in the pre-hospital setting [16,29-32]. Second, the ambulance services in Victoria, Western Australia and South Australia are well placed to undertake large clinical trials. The paramedics in these states are highly trained and able to successfully enrol patients using a computer-generated envelope randomisation strategy, and then implement the required treatment. Third, the ethical issues associated with non-consent randomisation of unconscious patients have been carefully considered by Ethics Committees in each of the states. Our approach of delayed or non-consent has been accepted in the previous trials cited above. There is now a framework under the NHMRC that supports the conduct of such trials.

There will be important differences between the study protocol in Victoria, Western Australia and South Australia owing to variations in standard operating procedures and for this reason a stratified randomisation approach has been adopted. Ambulance Victoria has a different staffing structure whereby cardiac arrests are attended by intensive care paramedics with a wider scope of practice for airway intervention (intubation) and drug administration.

The Victorian ambulance protocol allows for endotracheal intubation while the South Australia and Western Australian protocols allow for the use of either endotracheal intubation or laryngeal mask airway. In addition, the Victorian ambulance protocol allows the administration of midazolam 2-5 mg IV and pancuronium 8 mg for sedation of patients in the post resuscitation phase as a treatment option for patient shivering. This will not be part of the Western Australia and South Australia protocol, thus we will be able to ascertain the prevalence of overt shivering following the infusion of cold fluids by the paramedics. Thus, we will be able to assess whether the suppression of shivering is important in the induction of therapeutic hypothermia by the measurement of temperature at hospital arrival.

There is an urgent need to improve outcomes from out-of-hospital cardiac arrest. The RINSE trial will test the effect of administration of a bolus of 20 mL/kg of ice cold saline during CPR on patient survival. If this simple, inexpensive treatment is found to improve patient outcomes it will be an important prehospital intervention globally.

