### Study sites

This is a three-centre funded study administered centrally through the Monash University Department of Epidemiology and Preventive Medicine with study sites in Victoria (Victoria Ambulance and Monash University); South Australia (South Australia Ambulance Service and Flinders University) and Western Australia (St John Ambulance and University of Western Australia). In Victoria, only MICA paramedics will enroll patients whereas in WA and SA all paramedics (but not transport officers) will recruit patients.

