### Study Treatments

For patients randomised to paramedic cooling:

- Standard advanced cardiac life support

- Advanced Airway (Endotracheal Tube/Laryngeal Mask Airway) and ventilation with 100% oxygen

- Infuse 20 mL/kg cold fluid via IV stat during CPR

- Measure temperature using tympanic probe

- If temperature > 34.5°C, infuse further 10 mL/kg stat

- After ROSC, infuse further 10-20 mL/kg (to a maximum of 2 litres total fluid) ice-cold saline

- If shivering occurs post resuscitation, administer midazolam 2-5 mg IV and pancuronium 8 mg (Victoria only)

For patients randomised to hospital cooling:

- Standard advanced cardiac life support

- Advanced Airway (Endotracheal Tube/Laryngeal Mask Airway) and ventilation with 100% oxygen

- Measure temperature using tympanic probe

- Insert IV line and administer drugs as per protocol

- Fluid challenge with standard temperature saline only as per current patient care guideline

- Post resuscitation: midazolam 1-5 mg only to maintain intubation as needed

- Pancuronium 8 mg only if intubation unable to be maintained with midazolam (Victoria only)

After arrival at the Emergency Department, all patients receive standard care which may include cooling to 33°C for 24 hours.

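### The Discussion says the trial can assess whether suppressing shivering matters, but suppression is not randomised and no available comparison identifies its effect

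*Protocol article*

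**What the plan says.** The Discussion of the protocol article sets out how practice varies between the states and then draws two conclusions.

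- The variation is acknowledged: "There will be important differences between the study protocol in Victoria, Western Australia and South Australia owing to variations in standard operating procedures". It includes Victoria's different staffing, its wider scope of practice for airway and drugs, and different airway options.
- Shivering drugs are tied to Victoria: "the Victorian ambulance protocol allows the administration of midazolam 2-5 mg IV and pancuronium 8 mg for sedation of patients in the post resuscitation phase". They are an option there when a patient shivers.
- Their absence elsewhere is then used: "This will not be part of the Western Australia and South Australia protocol, thus we will be able to ascertain the prevalence of overt shivering". From this the article concludes that "we will be able to assess whether the suppression of shivering is important in the induction of therapeutic hypothermia". The yardstick it names is the temperature recorded when the patient reaches hospital.

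Other sections bear on the point.

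- Study sites: "In Victoria, only MICA paramedics will enroll patients whereas in WA and SA all paramedics (but not transport officers) will recruit patients".
- Study Treatments, cooling arm: "If shivering occurs post resuscitation, administer midazolam 2-5 mg IV and pancuronium 8 mg (Victoria only").
- Study Treatments, hospital-cooling arm: "Post resuscitation: midazolam 1-5 mg only to maintain intubation as needed". In Victoria only, pancuronium may follow if midazolam does not suffice for that purpose.
- Randomisation: the allocation is cooling during CPR or standard treatment, in blocks of ten, stratified by state because paramedic skills and hospital treatment may differ.

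**The concern.** The first conclusion, that the prevalence of overt shivering can be described where no drug suppresses it, is descriptive and raises no difficulty. The second is causal. It says the trial can judge whether suppressing shivering matters for inducing hypothermia. That needs a comparison of suppressed with unsuppressed patients who are otherwise alike, and the trial does not allocate suppression.

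Arrival temperature is a declared secondary outcome in the Abstract, so the data for such a comparison will exist and the published statement invites someone to make it. A difference between states in arrival temperature could then be read as an effect of suppression when it reflects crew, airway practice, how the cooling was delivered, or which patients reached hospital.

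**Working it through.** No figure is attached to the shivering statement. The article's design figures (603 and 653 per arm) concern survival at discharge. They reproduce with a two-sided 0.05 test, 80% power and a continuity correction, but have no bearing here. The check is therefore one of identification: can any comparison in this design isolate suppression?

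**Inputs.** Three states (Victoria V, Western Australia W, South Australia S); two randomised arms (cooled 1, control 0); suppression of shivering available only to cooled patients in V (Study Treatments and Discussion).

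**1. Victoria against WA/SA, cooled patients only.** Columns: intercept, indicator of V, indicator of W, suppression. Over the three states, suppression takes the values 1, 0, 0, the same as the indicator of V. That is 4 columns with rank 3. Suppression is aliased with state.

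**2. Victoria against WA/SA, using randomised controls.** The state-by-arm model has 6 columns (intercept, V, W, arm, V×arm, W×arm) and rank 6, one per cell. Suppression equals V×arm, so adding it gives 7 columns and still rank 6.

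The same in symbols: let D be the cooled-minus-control difference in arrival temperature in a state, δ the effect of cooling there without suppression, and σ the effect of having suppression available. Then

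- D(V) = δ(V) + σ
- D(W) = δ(W)
- D(S) = δ(S)

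This is three equations in four unknowns. The contrast an analyst would compute is

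D(V) − [D(W) + D(S)]/2 = σ + {δ(V) − [δ(W) + δ(S)]/2}.

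State main effects have gone, which is a real gain, but the term in braces stays.

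**3. What would make it estimable.** If δ is assumed equal in all three states, the model is intercept, V, W, arm and suppression: 5 columns, rank 5, and the term in braces is zero. The article does not state that assumption, and its own list of state differences makes it doubtful.

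**4. Control-arm drugs.** Victorian controls may receive midazolam and pancuronium to maintain intubation. If those drugs shift arrival temperature in Victorian controls by τ, then D(V) = δ(V) + σ − τ, and the contrast no longer isolates σ even with equal δ. Midazolam in WA/SA controls would add similar terms.

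**5. Within Victoria.** State is held constant, but the drugs are given when shivering occurs. Treated and untreated patients differ in whether they shivered, so the comparison is confounded by indication.

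**6. Within WA/SA.** Patients who shiver can be compared with those who do not, but none is suppressed. This is an observational association of shivering with temperature, not an effect of suppression.

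**7. Who has the outcome.** Arrival temperature exists only for patients who reach hospital. Data Safety Management says most patients die at the scene or in hospital, and Sample Size expects return of circulation in VF patients to rise from 40% to 45% with cooling. The measured group is thus a post-randomisation subset that the plan itself expects to differ by arm, and it may differ by state.

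**The case against.** The strongest reply is that the article names no comparison. A reader might infer that it commits to a raw Victoria v WA/SA contrast; it does not. The passage can also be read as a question within WA/SA: how often do unsuppressed patients shiver, and do shiverers arrive warmer? If overt shivering proved rare, suppression could hardly matter much, and no comparison between states would be needed. Part of this stands. The contrast is inferred, and a low prevalence would be informative. But that reading gives no answer if shivering is common, is itself non-randomised, and includes nobody whose shivering was suppressed. It supports the prevalence statement, not the conclusion drawn from it.

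Second, a reader might say that suppression and state cannot be separated at any sample size. That is too strong as an unconditional statement. Step 3 shows that the effect is estimable if cooling works equally across states apart from suppression, and WA against SA offers some gauge, from one pair of states, of how far states sharing a policy differ. The inference is assumption-dependent, and the assumption is unstated.

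Third, it is tempting to read the midazolam lines as contradicting each other, because the control-arm line carries no state limit while the Discussion excludes WA and SA. They do not conflict. One concerns maintaining intubation in controls; the other concerns treating shivering with midazolam plus pancuronium. They cover different indications and need no reconciliation.

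Fourth, shivering is neither an aim nor a listed outcome, and a condensed article may leave exploratory analysis details to a fuller document. That is fair as to details. The point here is an affirmative claim in print, not an omission.

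**Conclusion.** The concern holds in a limited form: the Discussion promises a conclusion that the design does not identify. Between states, suppression is aliased with state (4 columns, rank 3) or, with controls, with the Victoria-by-cooling interaction (7 columns, rank 6). It is recoverable only under an otherwise equal cooling effect across states, and then only if control-arm sedation or paralysis does not disturb arrival temperature. Comparisons within Victoria or within WA/SA do not rescue it. No size in degrees can be given, because the documents contain no arrival temperatures or shivering rates.

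A reader might infer that the state differences also undermine the trial's main result. The documents do not support that: randomisation is stratified by state, which keeps cooling against control a randomised comparison within each state, and nothing in the survival outcome, the sample sizes or the interim rule depends on shivering. The statement about prevalence in WA/SA also stands.

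**What to change.** Delete the claim, or restate it as exploratory, for example:

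> Exploratory: the prevalence of overt shivering in WA and SA will be described, and the cooling-minus-control difference in arrival temperature will be compared between Victoria and WA/SA (arm-by-state interaction). Any difference cannot be attributed to shivering suppression.

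Alongside it:

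- report, by arm and state, how many patients reached hospital and had a temperature recorded;
- note that these patients are a post-randomisation subset, so the arm difference in temperature is itself open to selection;
- note that Victorian controls may also have received sedation or paralysis.

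The cost is a change of wording, one exploratory analysis on data already planned, and one weaker claim. Sample size, treatment and the primary analysis do not change.
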